**Figure 3 Fig3:**
[figure not shown]
**Details of experimental setup.** Two straps over the acromion -one attached directly to the chair and one attached to the support of a load cell **(A)**; Force and electromyography activity (**(B)** surface electrode) of the upper trapezius muscle will be measured simultaneously during shoulder elevation movements. Feedback will be provided from the projection of a 20-inch screen on a white wall in front of the subject.

The maximum value in Newtons (N) will be considered the MVC. After three minutes of rest following the last MVC, the first sEMG signal (EMG-1) will be collected. The volunteer will be instructed to perform a ‘step contraction’, consisting of five force levels (10, 15, 20, 25 and 30% MVC). To investigate possible myoelectric manifestations of fatigue, a repetition of the third step (20% MVC) will be added as the sixth step to determine differences in the sEMG variables between these two steps [22]. Contraction time will be 11 seconds for each force level. Feedback of the step contraction will be provided from the projection of a 20-inch screen on a white wall in front of the subject. All participants will receive training prior to the shoulder elevations, based on the previously determined force levels.

New evaluations of pain and cervical range of motion (EV2) will be performed after one minute of rest. Acupuncture will then be performed, with the needles remaining inserted for 30 minutes. After the removal of the needles, further evaluations of pain and cervical range of motion will be performed (EV3), followed by a second EMG reading (EMG-2) in the same manner as performed during EMG-1. A fourth evaluation of pain and cervical range of motion (EV4) will be performed after two minutes of rest.

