### Sample size calculation

The sample size was calculated considering α = 0.05 (5% chance of type one error) and 1-β = 0.99 (% of power of the sample), and data on the amplitude of the EMG signal in the study by Chou *et al*. [26]. The values used were those described by Chou et al. [26] in the period prior to acupuncture (21.3 ± 9.5 μV) and after three minutes of needle manipulation in the acupoints TE-5 and LI-11 (9.5 ± 3.5 μV). The minimum number for each group was determined to be 12 individuals (total = 24).

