### Data analysis

Linear regression analysis will be applied for each individual to investigate associations between the sEMG variables and force (excluding the sixth step). The slopes of the regression lines will be used to measure the sensitivity of the sEMG variables regarding changes in force. The Shapiro-Wilk test will be used to test the normality of the data distribution regarding RMS and MDF values in the third and sixth step of the step contraction. Paired samples (Student’s t-test or Wilcoxon test) will be used to test differences between third and sixth contraction step. A mixed linear model will be used to analyze and compare the slopes of the regression lines during sustained contraction (five steps) between pre-acupuncture (EMG-1) and post-acupuncture (EMG-2) evaluations. These comparisons will demonstrate whether acupoints TE-5 and LI-11 affect the activity of the upper trapezius muscle, as hypothesized. The pain (numerical rating scale and pain area) and cervical range of motion data collected during the four evaluations will also be compared using a mixed linear model. The Statistical Package for Social Sciences (**IBM SPSS Statistics**, version 20.0, IBM™, Armonk, New York, United States) for Windows) will be employed for the statistical analysis, with the level of significance set to 5% (*P* <0.05).

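### The EMG model uses the pre-needling reading only as a level of the outcome; adjusting the tACP–sACP comparison for it is a cheap efficiency gain whose size depends on figures the article does not give

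*Protocol article*

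**What the plan says.** All references are to the protocol article.

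- **Experimental procedures.** Before needling, "the first sEMG signal (EMG-1) will be collected". After 30 minutes of needling, EMG-2 is recorded in the same way. EV1 and EV2 (pain and range of motion) precede needling; EV3 and EV4 follow it.
- **Outcome measures.** The primary outcome is upper trapezius EMG activity after a single session.
- **Data analysis.** Each person's sEMG variables are regressed on force, and a mixed linear model is used to "compare the slopes of the regression lines during sustained contraction (five steps) between pre-acupuncture (EMG-1) and post-acupuncture (EMG-2) evaluations". These comparisons are said to show whether the acupoints act on the muscle. For the secondary outcomes, pain and "cervical range of motion data collected during the four evaluations will also be compared using a mixed linear model". The section names no covariate, treatment contrast, period or sequence term, or constraint on the baseline means.
- **Sample size calculation.** The inputs are EMG amplitudes from an outside study, "in the period prior to acupuncture (21.3 ± 9.5 μV) and after three minutes of needle manipulation" at the same two points (9.5 ± 3.5 μV), with 99% power, giving 12 per group.

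**The concern.** Each person has two sessions, each with a pre-needling and a post-needling EMG. The question of interest in a sham-controlled crossover is whether EMG-2 differs between tACP and sACP within a person. EMG-1 cannot be affected by that session's needling, so its natural use is to explain variation in EMG-2.

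When EMG-1 is instead a freely estimated level of the outcome, the treatment-by-time interaction with complete data equals the EMG-2 minus EMG-1 change under tACP, less the same change under sACP. That fixes the baseline coefficient at 1. If the within-person regression of EMG-2 on EMG-1 is flatter than 1, the subtraction over-corrects and enlarges the variance of the contrast. With 12 people per group, a real difference from sham is then more likely to be missed. This is separate from whether the contrast is named: adding an unconstrained interaction to the stated model would still give change scores.

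**Working it through.** **The plan's own figure.** The difference is 21.3 − 9.5 = 11.8 μV and the pooled SD is √[(9.5² + 3.5²)/2] = 7.16 μV. The two-sample normal formula at 99% power is n = 2(z₁ + z₂)² × 7.16² / 11.8².
- One-sided 5%: 2 × (1.645 + 2.326)² × 51.25 / 139.24 = 11.6, so 12. This matches.
- Two-sided 5%: 2 × (1.960 + 2.326)² × 51.25 / 139.24 = 13.5, so 14.
- A two-sided paired t-test also gives 12 if the before–after correlation is 0.5, which is an assumption.

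This 99% refers to a before–after change in amplitude. It is not the power of a tACP–sACP comparison of slopes.

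**The two estimators.** For each person let DX and DY be the tACP-minus-sACP differences in EMG-1 and EMG-2, with SDs sx and sy and correlation r.
- Change score: variance sx² + sy² − 2r·sx·sy, with 10 residual df at n = 12 with a sequence term.
- EMG-1 as covariate: variance sy²(1 − r²), with 9 df and a further small-sample factor of about 1 + 1/9.

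With sx = sy the large-sample ratio of covariate to change score is (1 − r²)/[2(1 − r)] = (1 + r)/2. That is 0.50 at r = 0, 0.75 at 0.5, 0.85 at 0.7 and 0.90 at 0.8. At r = 0.8, 0.90 × 10/9 = 1.00, so at n = 12 the advantage is used up.

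**Assumptions for power.** None of these is in the article: two-sided 5%; true tACP–sACP difference 5.9 μV (half of 11.8); the amplitude SDs standing in for slope SDs; between-session correlation 0.3–0.5; within-session before–after correlation 0.5–0.9. The design is n = 12 with six per sequence, and power is from simulation.

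*Central case: between-session correlation 0.5 (also used for before–after pairs across sessions), within-session 0.75.*
- All SDs 9.5: sx² = sy² = 2 × 90.25 × 0.5 = 90.25; covariance 2 × 90.25 × 0.25 = 45.13; r = 0.5. SD of change score √90.25 = 9.5; with covariate √(90.25 × 0.75) = 8.2. Power 49% v 55%.
- After-SD 3.5 under tACP only (sham 9.5): sy² = 12.25 + 90.25 − 33.25 = 69.25; covariance 9.5 × 0.25 × 13 = 30.9; r = 0.39. SDs √97.75 = 9.9 and √(69.25 × 0.85) = 7.7. Power 47% v 61%.
- After-SD 3.5 in both sessions: sx² = 90.25, sy² = 12.25, covariance 2 × 33.25 × 0.25 = 16.6; r = 0.5. SDs √69.25 = 8.3 and √(12.25 × 0.75) = 3.0. Power 60% v more than 99%.

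*Across the assumed range (change score v covariate).*

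| Before / after SDs (μV) | Power | Gain |
|---|---|---|
| Equal at 9.5, r = 0.3 to 0.5 | 29% v 37%; 42% v 51%; 49% v 55% | 6 to 9 points |
| Equal at 9.5, r near 0.7 | 71% v 71% | about nil |
| Equal at 9.5, r = 0.8 | 87% v 86% | loss of about 1 point |
| 9.5 before; after 3.5 tACP, 9.5 sham | 31–66% v 51–75% | about 10 to 20 points |
| 9.5 before; after 3.5 in both sessions | 41–75% v 99–100% | larger |

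Type I error was about 5% for both estimators throughout. If the effect is instead scaled so that the change score has 80% power with equal SDs, the covariate gives 95.5% at r = 0, 86% at 0.5, 81% at 0.7, 79% at 0.8 and 77% at 0.9.

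**Sensitivity to the assumed effect.** At 11.8 μV in the central case, power is 97% v 98% with equal SDs and 96% v 99% if only tACP shrinks the SD. At the lowest correlations in the latter scenario it is 83% v 97%.

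**The case against.** The strongest reply is that the article states no treatment comparison, so the estimator criticised here is inferred. A mixed model with pre-needling means constrained equal across treatments would also fit the text. That constraint is natural because EMG-1 precedes needling and the order is randomised. It keeps EMG-1 as an outcome level with variance sy²(1 − r²), so nothing is lost. A condensed article may leave such detail to a fuller document. All of this stands, and it is why the point is conditional. What remains is that the text does fix EMG-1 and EMG-2 as compared levels and says nothing that would prevent the change-score reading.

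A second reply concerns the SDs, and it also stands. A reader might infer from 9.5 and 3.5 μV that the baseline coefficient cannot exceed 3.5/9.5 = 0.37, that the contrast carries the whole noise of two baselines, and that power falls to 41–75% when 99–100% is available. The documents do not support this:
- The SDs are amplitudes from an outside study after three minutes of manipulation. The analysed variables are slopes of RMS and MDF on force after 30 minutes of needling, and no slope SD is given.
- The 41–75% range also needs sham to shrink the SD exactly as real needling does, and there is no sham figure.
- Noise from both baselines enters in full only at r = 0. With equal SDs and r = 0.5, the change score is no noisier than using EMG-2 alone.

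Third, the described procedure suggests that EMG-1 and EMG-2 share one electrode and strap set-up within a session. That could push r upward, where the gain vanishes. This is plausible, but no value is given.

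Finally, modelling EV1 to EV4 as four levels is a legitimate choice, since EV2 follows the step contraction and the model can show its effect.

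**Conclusion.** The point holds as an efficiency improvement. EMG-1 enters the stated model only as a compared level. If the tACP–sACP comparison is taken from it as an unconstrained interaction, it is a difference of change scores, which is usually less efficient than baseline adjustment.

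At n = 12 and an assumed 5.9 μV, the gain from adjustment is about 6 to 9 power points with equal SDs and r of 0.3 to 0.5. It is nil near 0.7, and there is a loss of about 1 point at 0.8 and somewhat more at 0.9 and above. It is about 10 to 20 points if only real needling shrinks the SD, and larger only if 9.5 and 3.5 μV held for the slopes in both sessions. Every one of these figures rests on inputs the article does not state.

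It would be wrong to infer that the analysis is invalid or that a particular power loss has been shown. The change-score estimator is unbiased and its type I error is correct. The absence of a named tACP–sACP contrast is the more basic gap, and the two are best settled together. For pain and range of motion no gain has been quantified.

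**What to change.** In Data analysis, state the tACP–sACP contrast for the EMG slopes and how EMG-1 enters it. Either of these will do:

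1. One record per participant and session, with the EMG-2 slope as response; treatment, period and sequence as fixed effects; participant as random effect; and the same session's EMG-1 slope as a covariate. Split the covariate into the participant's mean over both sessions and the session's deviation from that mean, so that the within-person contrast uses the within-person coefficient.
2. Keep EMG-1 and EMG-2 as outcome levels, but constrain the pre-needling means to be equal across treatments. In large samples this has the same efficiency.

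Optionally, treat pain and range of motion in the same way, with EV3 and EV4 as responses and the session's pre-needling readings as baseline.

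The cost is wording only, with no new data. The covariate uses one residual degree of freedom (10 to 9 at n = 12). With equal SDs this costs about 1 power point at r = 0.8 and somewhat more at 0.9 and above.

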**Methods/Design:**

A total of 12 patients with nonspecific neck pain and 12 healthy subjects will be enrolled in a randomized, single-blind crossover study. Each subject will receive two forms of treatment in random order: a single session of traditional acupuncture (acupoints: triple energizer 5, ‘*Wai-guan*’ and large intestine 11, ‘*Qu-chi*’) and sham acupuncture. To eliminate carry-over treatment effects, a one-week wash-out period will be respected between sessions. Surface electromyography will be used to determine motor control in the upper trapezius muscle before and after treatment. The outcome measures in the group with neck pain will be a numerical pain rating scale (range: 0 (no pain) to 10 (maximum pain)), documentation of the pain area on a body chart and cervical range of motion. Comparisons before and after acupuncture treatment will demonstrate whether acupoints affect the activity of the upper trapezius muscle, pain and cervical range of motion.

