## Methods/Design

### Overview of research design

A randomized, single-blind, sham-controlled, crossover clinical trial will be carried out. The crossover design will be used to exclude the potential interference of individual differences. Figure 1 displays the flow of the study.

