### Randomization and blinding

Each patient will receive two forms of acupuncture in random order: a single session of traditional acupuncture (tACP) and sham acupuncture (sACP). To eliminate carry-over treatment effects, a one-week wash-out period between the treatments will be respected. Randomization in each group will be performed by lots using opaque envelopes containing either the letter A, corresponding to tACP, or B, corresponding to sACP. The participants in each group will be distributed in two subgroups of six individuals based on the initial treatment (tACP and sACP), as shown in Figure 1. When one of the subgroups has completed the treatment course, the order of consecutive arrival of the volunteers will be used until all individuals have been allocated.

Measurements will be performed by five independent researchers. Researcher one will be in charge of the screening process, administration of the questionnaire and randomization of the treatments. Researcher two will be in charge of collecting the EMG data. Researcher three will administer the acupuncture treatment. Researcher four will be in charge of the analysis and processing of the EMG data. Researcher five will be in charge of the statistical analysis of the EMG, pain and cervical range of motion data. The participants will be blinded to the type of treatment and will not be informed that one of the two treatments is a sham procedure. Researchers four and five will also be blinded to both the group allocation and type of treatment.

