### Outcome measures

The primary outcome of the study is the EMG activity of the upper trapezius muscle after a single session of acupuncture. The secondary outcomes for the study are the numerical rating scale score for pain, pain area and cervical range of motion.

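### The article names only before-after contrasts as its test of the acupoint effect; the traditional-versus-sham difference in change that the randomised crossover was built to estimate is not stated

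*Protocol article*

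**What the plan says.** The Overview of research design states: "A randomized, single-blind, sham-controlled, crossover clinical trial will be carried out". Under Randomization and blinding, every participant receives both tACP and sACP in random order, a week apart. Each group (neck pain and healthy control) is split six and six by which treatment comes first.

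Under Outcome measures: "The primary outcome of the study is the EMG activity of the upper trapezius muscle after a single session of acupuncture". Sham is not mentioned there.

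The Data analysis section names three comparisons:

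- step 3 against step 6 of the contraction, by a paired t-test or Wilcoxon test;
- for the EMG slopes, a mixed linear model to "compare the slopes of the regression lines during sustained contraction (five steps) between pre-acupuncture (EMG-1) and post-acupuncture (EMG-2) evaluations";
- for pain and cervical range of motion, data "collected during the four evaluations will also be compared using a mixed linear model".

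After the slope comparison it draws the inference: "These comparisons will demonstrate whether acupoints TE-5 and LI-11 affect the activity of the upper trapezius muscle, as hypothesized". The Abstract (Methods/Design) says the same of all outcomes: "Comparisons before and after acupuncture treatment will demonstrate whether acupoints affect the activity of the upper trapezius muscle, pain and cervical range of motion".

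The Sample size calculation uses a pre-needling and a post-needling EMG amplitude from an earlier study. It gives no sham figure.

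**The concern.** In this design, randomisation and the sham session protect one contrast: the change under tACP against the change under sACP in the same person. A before-after contrast has no such protection, because the two recordings differ in more than needling. By the Experimental procedures, EMG-1 follows maximal contractions and three minutes of rest. EMG-2 follows the first step contraction, 30 minutes with needles in place and a further round of pain and neck-movement testing. Rest, repetition of the task and expectation can move the readings under either treatment.

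The sham session exists to subtract such changes. If the before-after comparison decides the hypothesis, they are not subtracted, and a significant result would not show that TE-5 and LI-11 do more than sham. This goes beyond a term left out of a condensed article, since the text says which comparison answers the hypothesis, and it is the wrong one.

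**Working it through.** **1. What each contrast estimates.** Let δ be the non-specific change from EMG-1 to EMG-2, equal in both sessions, and τ the specific effect of tACP over sACP.

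- Before-after within tACP sessions: δ + τ.
- Before-after pooled over both sessions: [(δ + τ) + δ]/2 = δ + τ/2.
- Difference in change, tACP minus sACP: (δ + τ) − δ = τ.

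Only the third is free of δ. The pooled version also halves a true effect.

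**2. The plan's own figure.** Inputs from Sample size calculation: 21.3 ± 9.5 μV before, 9.5 ± 3.5 μV after, α = 0.05, power 0.99, stated result 12 per group.

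- Difference: 21.3 − 9.5 = 11.8 μV.
- Pooled SD: √[(9.5² + 3.5²)/2] = 7.16 μV.
- Two-means formula, n = 2 × SD² × (z_α + z_β)² / difference²: 12 one-sided, 14 two-sided.
- Two-sided paired t-test with an assumed pre-post correlation of 0.5: SD of change √(9.5² + 3.5² − 2 × 0.5 × 9.5 × 3.5) = 8.32 μV, which also gives 12.

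The stated 12 is reproduced, and each route to it uses a pre-post difference. Planning and analysis therefore rest on the same contrast.

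**3. Illustration of misattribution.** Two-sided paired t-test, n = 12, 11 df, τ = 0. Drift is in SDs of the within-session change and is assumed. The noncentrality is drift × √12.

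| Assumed shared drift (SD) | Noncentrality | P(significant) |
|---|---|---|
| 0.3 | 1.04 | 0.158 |
| 0.5 | 1.73 | 0.353 |
| 0.7 | 2.42 | 0.599 |
| 1.0 | 3.46 | 0.883 |

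In the units of the sample size inputs, with pre-post correlation from 0 (SD of change 10.12) to 0.5 (SD 8.32):

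| Assumed non-specific change (μV) | P(significant) |
|---|---|
| 0 | 0.05 |
| 2.95 | 0.15 to 0.20 |
| 5.9 | 0.45 to 0.61 |
| 11.8 | 0.96 to 0.99 |

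When the drift is equal under both treatments, the tACP-sACP contrast holds 0.05 in every row.

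**4. What the treatment contrast would cost in power.** The SD of the difference in changes is SD of change × √[2(1 − ρ)], where ρ is the correlation of changes between periods. The article gives no sham change, so the sham change, the pre-post correlation (0 or 0.5) and ρ (0 or 0.5) are all assumptions. Two-sided α is 0.05. Power with 12 uses 10 df to allow for a period adjustment.

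| Sham change | Net effect (μV) | N per group for 99% | Power with 12 |
|---|---|---|---|
| none | 11.8 | 12 to 30 | 0.73 to 0.99 |
| half of 11.8 | 5.9 | 39 to 111 | 0.25 to 0.60 |
| three quarters of 11.8 | 2.95 | 149 to 435 | 0.10 to 0.20 |

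These are amplitudes, whereas the planned analysis is of slopes, so the table shows direction and rough scale only.

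**The case against.** The strongest reply is that the article lists no model terms at all, and these are commonly left to a full protocol or analysis plan. A mixed linear model can carry treatment as a factor, and there are hints that it might. A simple paired test is kept for step 3 against step 6 while the slopes get a mixed model. The statistical analyst is blinded to type of treatment. The crossover is justified as removing individual differences.

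This stands in part. A reader might infer that the trial will never test tACP against sACP and that the sham data go unused; the article does not show that. What it does show is that the only contrast named is before-after and that this contrast is said to answer the hypothesis. A later plan with a treatment term would still leave that inference wrong in print.

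A reader might also take 35%, 60% and 88% as the error rates of the planned analysis. They are not. They belong to a paired t-test in 12 people with a drift size that no document gives, whereas the plan has a mixed model, 24 participants and two sessions each.

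Regression to the mean is another tempting argument, because neck pain patients enter with a pain score of 3 to 6. It has little force here. Nobody is selected on EMG, and regression from a screening score would mostly occur before the evaluations on either side of needling. Learning is also tempered by the training given beforehand. Whether maximal contractions are repeated before EMG-2 cannot be judged without Figure 2.

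**Conclusion.** The point holds as a fault in the stated inference rule. In a randomised, sham-controlled crossover, the article assigns the acupoint conclusion to a before-after comparison and nowhere states a tACP-sACP contrast, a period term or a sequence term. The conclusion it promises does not follow from the comparison it names.

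The size depends on the non-specific change, which is unknown. With none, the before-after test keeps its 5%. With a shared drift of half an SD or more, the illustrative paired test is significant in over a third of trials in which acupuncture does nothing beyond sham. The 5% for the tACP-sACP contrast assumes the drift is the same under both treatments.

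**What to change.** - **Primary test.** State it as the tACP-minus-sACP difference in the EMG-2 minus EMG-1 change in slope. In the mixed model this is the treatment-by-time term, with fixed effects for period and sequence and a random subject effect. Say which EMG variable (RMS or MDF) and which group is primary, since two variables in two groups otherwise give four candidate tests.
- **Pain and range of motion.** Test the treatment difference in change in the same way. The EV2-to-EV3 change is the natural contrast because it brackets the needling. How EV1 and EV4 are used is a matter of choice.
- **Wording.** Rewrite the inference sentences in the Abstract (Methods/Design) and Data analysis so that the acupoint conclusion rests on the treatment contrast.
- **Sample size.** Either say that the 12 per group and 99% power apply to the pre-post change only, or restate them for the new contrast with an explicit sham assumption.
- **Needling description.** The Acupuncture section ties on-point needling to the neck pain group and off-point, superficial needling to the control group. Randomization and blinding gives both treatments to everyone. These sections must be reconciled so that the tACP-sACP contrast is defined in both groups.

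The cost is mainly text. The design already schedules both sessions for every participant, so no visit or measurement is added. The real price is that power for the contrast of interest may be well below 99%. Trial status says recruitment is under way, so the change should be fixed and dated before treatment codes are opened.
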